#### Other study parameters

Other parameters including clinical and psychosocial patient characteristics, breast-cancer treatment related variables, and compliance with the psychological intervention are assessed at the time points shown in Table 2.

**Table 2 Tab2:** Parameters and assessment time points

Parameters	Instrument	T 0	T1	T2	T3	T4
Pain operated breast	NRS	x	x	x	x	x
	Pain localization	x		x	x	x
	BPI [60]	x		x	x	x
	DN4 [59]	x	x	x	x	x
Pain unrelated to BC treatment elsewhere	NRS	x		x	x	x
	Localization	x		x	x	x
Shoulder function	DASH [63]	x			x	x
Pain sensitivity	CPM	x	x		x	
	QST	x			x	
Pain catastrophizing	PCS [54]	x		x	x	x
Anxiety	HADS-A [52]	x		x	x	x
Depression	PROMIS short form v1.0 [64, 65]	x		x	x	x
Quality of life	EORTC-QLQ C30+BC [66]	x			x	x
Surgical fear	SFQ [67] & single item [16]	x				
Fear of recurrence	CARS [68]	x		x	x	x
Breast cancer characteristics	TNM, receptors, histological profile	x			x	
	non-related chronic pain complaints	x			x	x
	pain medication	x	x	x	x	x
	Sedative and antidepressive medication	x	x	x	x	x
Patient characteristics	BMI	x			x	x
	Comorbidity and intoxications	x				x
	Unspecific symptoms	x		x	x	x
Breast cancer treatment details	Type of surgery		x	x	x	x
	ICBN handling		x			
	Breast cancer treatment complications		x	x	x	x
	Radiotherapy			x	x	x
	Chemotherapy	x		x	x	x
	Hormonal therapy	x		x	x	x
Anesthesia	Perioperative regional techniques		x			
	Acute pain day 0–7		x			
Patient compliance with protocol				x		

*T0* 1–3 weeks pre-surgery, *T1* postoperative week, *T2* 2 months follow-up, *T3* 6 months follow-up, *T4* 12 months follow-up. *NRS* numerical rating scale (0=no pain, 10=maximum pain), *BPI* brief pain inventory, *DN4* doleur neuropathique 4 questions, *CPM* conditioned pain modulation, *QST* quantitative sensory testing, *PCS* pain catastrophizing scale, *HADS* hospital anxiety and depression scale, *PROMIS* patient-reported outcomes measurement information system, *EORTC-QLQ* European Organization for Research and Treatment of Cancer Quality of Life Questionnaire, *SFQ* surgical fear questionnaire, *CARS* fear of cancer recurrence scale, *DASH* disability of the arm, shoulder and hand questionnaire, *BMI* body mass index, *ICBN* intercostobrachial nerve

#### Participant timeline {13}

The participant timeline is presented in Fig. 1

#### Sample size {14}

The sample size calculation has been performed for the primary outcome, the prevalence of PPBCT (NRS ≥ 3) at 6 months after surgery for breast cancer. The expected overall prevalence of PPBCT is 30%, but the high anxiety/high catastrophizing group, which we will recruit for the randomized trial, has been shown to have a 2.2 times higher prevalence [15, 16, 69], and we expect that about 30% of all patients will screen positive for anxiety/catastrophizing [16, 55, 70]. To be on the conservative side for our calculation, and in accordance with Burns and Moric, we estimate that the prevalence of PPBCT will be 50% in the high anxiety/catastrophizing group [71] and also that perioperative CBT decreases PPBCT prevalence by 50%.

For the current study, this would mean a reduction of the prevalence in the e-CBT group from 50 to 25%. We need to include 55 patients per group to obtain 80% power to detect this difference, with an alpha of 0.05. To account for a potential drop-out rate of 20%, we will recruit a total of 138 high anxiety/catastrophizing patients. All patients that are considered to have low anxiety/catastrophizing and thus are not randomized will be asked to participate in the cohort study. We expect to include around 322 low anxiety/catastrophizing patients based on an expected 30/70% ratio of high vs low anxiety/catastrophizing.

#### Recruitment {15}

Patients of participating hospitals with medium to high production volumes for breast cancer treatment are offered participation by their treating physicians. In addition, information about AMAZONE is shared on a website [64], on websites offering information about breast cancer treatment in the Netherlands, i.e., The Dutch breast cancer society (BVN), The Dutch Cancer Society (KWF), the Integraal Kankercentrum Nederland (IKNL), and also via social media. Hereby we aim to improve recruitment by patient empowerment.

### Assignment of interventions: allocation

#### Sequence generation {16a}

Allocation is performed using electronic stratified randomization with random permuted block sizes. Stratification factors are axillary dissection and center of inclusion.

#### Concealment mechanism {16b}

Patients in the e-CBT and EDU groups are blinded for the type of intervention. Patients in the TAU group cannot be blinded. Treating physicians have access to allocation information.

#### Implementation {16c}

Patients are enrolled by the treating physician at the participating centers. The allocation sequence is computer-controlled and generated by Castor® EDC.

### Assignment of interventions: blinding

#### Who will be blinded {17a}

Patients are only informed about allocation to either treatment (randomization) or control (TAU). Patients who will be randomized will not be informed about the type of intervention—e-CBT or EDU. The local AMAZONE teams can view the treatment allocation in the online patient administration program. Outcome analyses is performed by an independent statistician who will be blinded for the type of intervention.

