#### Procedure for unblinding if needed {17b}

The need for unblinding of participants is very unlikely as side effects of CBT are currently not described and EDU does not contain any information/advices that cannot be found elsewhere.

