### Data collection and management

#### Plans for assessment and collection of outcomes {18a}

Detailed information on outcomes is presented in the “Outcomes {12}” section. All investigators are working in accordance with GCP guidelines and are trained in the execution of clinical studies.

The teams of the centers assessing pain sensitivity by QST/CPM were trained to perform the standardized QST protocol according to the regulations of the German Research Network Neuropathic pain (DFNS) by the accredited location at the Center for Biomedicine and Medical Technology Mannheim (CBTM), Ruprecht-Karls-University Heidelberg, Medical Faculty Mannheim.

To maintain the quality of the measurements, refresher trainings are organized on a regular basis.

Preoperative risk profiling and all patient reported outcomes (questionnaires) as well as medical information and SAE reporting are collected online with the cloud-based clinical data management platform Castor® EDC (www.CastorEDC.com).

The members of the local AMAZONE study teams are trained to use the program for study flow logistics (Ldot©), Castor©, screening forms and other questionnaires that have to be completed at the respective time points.

Patients are instructed to use the online software by the local investigators during the inclusion procedure.

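### Local teams and treating physicians can see the arm, and no blinded tester is named for QST/CPM, which are examiner-dependent secondary outcomes compared between e-CBT and EDU

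*Protocol article*

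**What the plan says.** The protocol article treats blinding in two places. Under Concealment mechanism {16b}: "Patients in the e-CBT and EDU groups are blinded for the type of intervention", and two sentences later "Treating physicians have access to allocation information". Under Who will be blinded {17a}: "The local AMAZONE teams can view the treatment allocation in the online patient administration program", followed by "Outcome analyses is performed by an independent statistician who will be blinded for the type of intervention". No other blinded role is listed.

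Plans for assessment and collection of outcomes {18a} says who does the sensory testing: "The teams of the centers assessing pain sensitivity by QST/CPM were trained to perform the standardized QST protocol". It describes training and refresher courses, but not whether the tester knows the arm.

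The secondary endpoints under Outcomes {12} include QST before surgery and at 6 months, and CPM before surgery, at 1 week and at 6 months. The statistical section {20a} compares both between e-CBT and EDU by linear mixed-effects regression.

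**The concern.** QST and CPM are threshold tests run face to face. CPM, for example, rests on repeated pressure pain thresholds before and after a cold pressor test. The readings depend partly on how the tester instructs and encourages the patient and when the tester decides that a threshold has been reached. A tester who knows that the patient received the active program can, without intending to, move the result towards what is expected.

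These measurements carry the trial's mechanistic aim, namely whether e-CBT alters nociceptive transmission and endogenous pain inhibition. A difference between arms that could be explained by tester expectation would be hard to interpret. The article does not simply leave the matter open: it addresses blinding and grants access to local staff without excluding testers.

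**Working it through.** **1. Who can see the arm, and who measures what**

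| Role | Access to arm (article) | Contact with outcomes |
|---|---|---|
| Randomized patient | Not told e-CBT or EDU ({16b}, {17a}) | Reports pain NRS and questionnaires online |
| Independent statistician | Blinded ({17a}) | Analysis |
| Local AMAZONE team | Can view it ({17a}) | May contact patients about missing questionnaires ({18b}) |
| Center team performing QST/CPM | Not stated separately; no blinding named ({18a}) | Runs QST and CPM |
| Treating physician | Has access ({16b}) | No stated role in delivering the intervention |

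The fourth row is the gap. If the testers belong to the local AMAZONE team, they can see the arm. If they are separate, the article does not say so.

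**2. The plan's own sample size, used as an input**

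For 50% versus 25%, two-sided alpha 0.05 (sidedness assumed) and 80% power, the unpooled formula gives

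n = (1.960 + 0.842)² × (0.50 × 0.50 + 0.25 × 0.75) / 0.25² = 7.85 × 0.4375 / 0.0625 ≈ 55 per arm.

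With 20% dropout, 55 / 0.8 = 68.75, rounded up to 69 per arm, or 138 in total. Both figures match the article. Tester blinding does not alter them.

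**3. Illustration of what a tester effect could do**

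The documents give neither a bias size nor the number of patients who undergo QST/CPM, so both are assumed. Take one continuous measure, no true difference, n per arm, and a systematic shift of b standard deviations between arms caused by the tester. In a simple two-group comparison the test statistic is centered at

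m = b / √(2/n)

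and the two-sided false-positive rate is

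1 − Φ(1.96 − m) + Φ(−1.96 − m).

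| Shift b (SD, assumed) | n = 55 per arm: m | Rate | n = 30 per arm: m | Rate |
|---|---|---|---|---|
| 0 | 0 | 5% | 0 | 5% |
| 0.1 | 0.52 | 8% | 0.39 | 7% |
| 0.2 | 1.05 | 18% | 0.77 | 12% |
| 0.3 | 1.57 | 35% | 1.16 | 21% |

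The shift is an average over all tested patients. If only half were tested by someone who knew the arm, an individual effect of 0.2 SD would average 0.1 SD, and the rate with 55 per arm would be 8% rather than 18%.

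**The case against.** The strongest reply is that tester access is inferred. The article speaks of center teams that assess pain sensitivity and, separately, of local study team members trained on the study-logistics software. It never says that a tester opens the allocation screen, and the full protocol, which is not shown, may name a blinded tester. This stands as a limit on certainty. It does not remove the point, because {17a} is where such a safeguard would be expected and it lists only patients and the statistician.

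Some local access also has a plausible reason. The two programs run on different platforms (Karify for e-CBT, Qualtrics for EDU), patients who do not open sessions are reminded, and local investigators instruct patients in the software. That can justify access for whoever handles logistics. It does not justify it for a tester.

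Standardized QST training reduces variation in procedure, but it does not blind the tester.

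Four stronger readings are tempting, and the documents do not support them:

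- *Staff have no need to know the arm because the protocol says so.* The sentence in {17b}, "The need for unblinding of participants is very unlikely", concerns participants. It says nothing about what staff need.
- *Concealment is compromised because physicians who see past allocations also enroll* ("Patients are enrolled by the treating physician at the participating centers"). The sequence is computer-controlled, uses random block sizes, and is stratified by axillary dissection and center. Nothing says that an allocation is visible before enrollment, and entry to the randomized part is fixed by questionnaire cut-offs, which leaves little room for selection.
- *Time to opioid cessation is biased by unblinded prescribers.* No section says that the physicians with access decide when opioids stop.
- *Contacts about missing questionnaires unblind patients.* The article has automatic reminders by email and text and says that team members can contact patients. It describes no disclosure of the arm.

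**Conclusion.** The point holds in a limited form. As written, the plan gives local teams and treating physicians the allocation, has center teams perform QST/CPM, and names no blinded tester for outcomes that depend on the examiner and are compared between arms. The conclusion rests on reading {17a} together with {18a}, and on the absence of a tester-blinding rule in the full protocol.

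The size of any bias cannot be derived from the documents. The 7% to 35% range above is illustrative: it depends on assumed shifts of 0.1 to 0.3 SD, all in one direction, and on 30 or 55 tested patients per arm.

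The exposure is on secondary, mechanistic outcomes. The primary endpoint (NRS of 3 or more at 6 months) is reported by patients who are not told which program they have and is analyzed by a blinded statistician, so it is affected at most indirectly. A reader should not infer that the primary comparison is invalid.

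**What to change.** Amend {17a} and the access rights in the patient administration program as follows:

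- Hide the arm from whoever performs QST/CPM and state that testers are blinded.
- Hide it, where feasible, from treating physicians, or state why they need it.
- Limit the view to therapists and the staff who release platform access.
- Record any accidental unblinding of the tester before the 1-week CPM and before the 6-month QST/CPM.

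This needs a permission change and a short amendment to procedures. It should need no extra staff in principle, and sample size, endpoints and analyses are unchanged. The practical cost is that platform access and session reminders must be handled by the therapist, a coordinator or a local team member who does not test.

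The change comes late for some patients. The Trial status section reports 130 recruited at six sites, without separating randomized from TAU patients. Those already allocated cannot be re-blinded to staff, so tester blinding will be mixed. Tester blinding status should therefore be recorded for each QST/CPM session and reported with the results.

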#### Procedure for unblinding if needed {17b}

The need for unblinding of participants is very unlikely as side effects of CBT are currently not described and EDU does not contain any information/advices that cannot be found elsewhere.

### Data collection and management

#### Plans for assessment and collection of outcomes {18a}

Detailed information on outcomes is presented in the “Outcomes {12}” section. All investigators are working in accordance with GCP guidelines and are trained in the execution of clinical studies.

The teams of the centers assessing pain sensitivity by QST/CPM were trained to perform the standardized QST protocol according to the regulations of the German Research Network Neuropathic pain (DFNS) by the accredited location at the Center for Biomedicine and Medical Technology Mannheim (CBTM), Ruprecht-Karls-University Heidelberg, Medical Faculty Mannheim.

To maintain the quality of the measurements, refresher trainings are organized on a regular basis.

Preoperative risk profiling and all patient reported outcomes (questionnaires) as well as medical information and SAE reporting are collected online with the cloud-based clinical data management platform Castor® EDC (www.CastorEDC.com).

The members of the local AMAZONE study teams are trained to use the program for study flow logistics (Ldot©), Castor©, screening forms and other questionnaires that have to be completed at the respective time points.

Patients are instructed to use the online software by the local investigators during the inclusion procedure.

#### Plans to promote participant retention and complete follow-up {18b}

At the assessment time points, participants automatically receive reminders by email and text messages to fill in the online questionnaires. Members of the local study team can contact the participant if questionnaires are missing or incomplete. In case online questionnaires were not filled in at one time point, patients still receive notifications at the subsequent follow-up assessment times. All collected data will be used for final analyses, even if a participant does not complete follow-up.

#### Data management {19}

Data handling is according to the Dutch General Data Protection Regulation (AVG) and the Dutch Act on Implementation of the General Data Protection Regulation (UAVG). Data are retrieved and stored according to GCP guidelines in a coded fashion in a protected database (Castor® EDC). Subjects will receive a unique sequential study code that does not include any personal information. The coding key will be password protected and kept in each participating hospital, only accessible by the local study team.

An independent quality officer will monitor the study data according to GCP practice. Monitoring encompasses the verification of informed consent, inclusion and exclusion criteria, source data of the clinical parameters and (S)AE reporting, and will take place at the initiation of the study, after inclusion of 10 patients at a site and after inclusion of the last patient.

#### Confidentiality {27}

Information about potential and enrolled participants is documented in a local trial master file (TMF) that is accessible only to the local AMAZONE team. Signed consent forms are collected in a local file. The forms are saved for 15 years after the end of the trial at the study centers.

#### Plans for collection, laboratory evaluation and storage of biological specimens for genetic or molecular analysis in this trial/future use {33}

See the “Additional consent provisions for collection and use of participant data and biological specimens {26b}”; there will be no biological specimens collected.

### Statistical methods

#### Statistical methods for primary and secondary outcomes {20a}

All analyses will be performed according to the intention-to-treat principle. The main analyses focus on the comparison of the e-CBT and education (EDU) group. Exploratory comparisons concerning prevalence of PPBCT, acute postoperative pain, and pain-sensitivity with the no-intervention (low fear) group will also be made, using similar statistical techniques as described below for the two randomized groups.

#### Primary study parameter(s)

Group differences concerning the prevalence of PPBCT at 6 months follow-up will be reported stratified by treatment allocation. Comparisons between e-CBT and EDU will be made using logistic regression analysis, adjusted for the variables used to stratify randomization. The odds ratio (OR) including 95% CI and *p*-value will be reported.

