## Introduction

### Background and rationale {6a}

Persistent pain after breast cancer treatment (PPBCT) is highly prevalent [1]. In the acute phase following surgery, reconstructive surgery, radiotherapy, and chemotherapy, up to 50% of the patients suffer from pain [2, 3]. In around 30% (15–65%) of patients, this pain persists for 1 year or longer. Previously, it was thought that pain after mastectomy was mainly neuropathic, caused by damage to the intercostal brachial nerve (ICBN). However, pain may also originate from other sources such as lymphedema, scarring of tissues of the chest wall [4], or from muscle guarding [5]. Once chronic, PPBCT and secondary problems are difficult to treat and require a complex individualized multidisciplinary approach [6, 7]. The standard pharmacological treatment of PPBCT consists of antidepressants [8, 9], and capsaicin [10], but even though effective, intolerable side effects often limit (long-term) treatment. Interventional treatment options of PPBCT target the thoracic dorsal root ganglia, intercostal nerves [11], stellate ganglion [12], thoracic sympathetic chain [13], and fascia of the thoracic wall [14].

In the past decade, research has identified treatment- and patient-related factors increasing the risk for PPBCT. Treatment-related risk factors such as axillary lymph node dissection, radiotherapy, and intercosto-brachial nerve handling may directly increase tissue damage. Patient-related risk factors such as genetic haplotypes, young age, high BMI, pre-existing pain, high postoperative pain intensity, and psychological distress suggest a greater vulnerability of the nociceptive system that is prone to sensitization [15–18]. Quantitative sensory testing (QST) demonstrated the presence of central sensitization in patients with PPBCT [19–22]. Moreover, there is accumulating evidence that patients with persistent postsurgical pain have less efficient inhibitory modulation of afferent nociceptive signals [23–26].

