### Outcomes {12}

#### Main study parameter/endpoint

The main outcome of the study is the prevalence of significant PPBCT in the operated area at six months, defined as a score ≥ 3 on an 11-point numeric rating scale (NRS).

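### The primary logistic model leaves out the pre-surgical pain score of the operated breast, which is already collected; the comparison stays valid but gives up some precision

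*Protocol article*

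**What the plan says.** - **Model.** Primary study parameter(s): "Comparisons between e-CBT and EDU will be made using logistic regression analysis, adjusted for the variables used to stratify randomization". Sequence generation {16a} names the variables: "Stratification factors are axillary dissection and center of inclusion". The covariate set is therefore stated, and it contains no pain variable.
- **Endpoint.** Main study parameter/endpoint: "prevalence of significant PPBCT in the operated area at six months, defined as a score ≥ 3 on an 11-point numeric rating scale". The definition makes no reference to the score before surgery.
- **Baseline measurement.** Table 2 has a row "Pain operated breast", measured by NRS and marked at every time point including T0, which is "1–3 weeks pre-surgery".
- **Prognosis.** Background and rationale {6a} lists among the patient-related risk factors "pre-existing pain, high postoperative pain intensity, and psychological distress".
- **Eligibility.** The exclusion list rules out past breast cancer surgery or treatment, but not existing pain in the breast.
- **Other analyses.** Section {20b} plans no additional analyses. The one sensitivity analysis named, in section {11d}, concerns psychological or psychiatric treatment started after surgery.
- **Reporting.** The primary section gives prevalence by arm, and the OR with 95% CI and p-value.

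**The concern.** A patient who already scores 3 or more in the affected breast before surgery, and still does at six months, counts as a case exactly like one whose pain began after treatment. If such patients are more likely to be cases, the T0 score explains part of the outcome variation. Leaving it out of a logistic model then costs power. It also leaves the estimate open to whatever imbalance in T0 pain the randomization happens to produce, since the stratification does not control that variable.

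The sample size has little slack. The planned 55 per group is reached only with the unpooled variance formula. The covariate must also be chosen in advance: adding it after an imbalance has been seen would look data-driven.

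**Working it through.** **Step 1: the plan's own figure.** Inputs from Sample size {14}: 50% versus 25%, alpha 0.05 (taken as two-sided), power 80%, drop-out 20%.

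- Unpooled variance: n = (1.960 + 0.842)² × (0.50×0.50 + 0.25×0.75) / 0.25² = 7.85 × 0.4375 / 0.0625 = 54.94, so 55 per group. This reproduces the plan.
- Drop-out: 110 / 0.80 = 137.5, so 138. This also reproduces.
- With pooled variance the requirement is 58 per group, and power at 55 is 78.1%.

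The sample size itself is not in dispute.

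**Step 2: gain from a binary baseline-pain covariate.** The share of patients with T0 pain and its OR for the endpoint are assumed. Marginal rates are held at 50% and 25%, with 55 per arm, 4,000 simulated trials per row and a likelihood-ratio test of the arm term. The stratification factors are left out of both models.

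| Share with T0 pain | OR of T0 pain | Power without | Power with | Change (points) | Conditional OR for arm |
|---|---|---|---|---|---|
| 20% | 1 | 79.7% | 79.4% | −0.3 | 0.333 |
| 20% | 2 | 79.2% | 79.7% | +0.5 | 0.326 |
| 20% | 3 | 78.1% | 79.7% | +1.6 | 0.316 |
| 20% | 5 | 78.7% | 82.3% | +3.6 | 0.296 |
| 20% | 8 | 79.1% | 84.9% | +5.8 | 0.273 |
| 40% | 1 | 78.5% | 78.4% | −0.1 | 0.333 |
| 40% | 2 | 79.0% | 80.1% | +1.1 | 0.324 |
| 40% | 3 | 78.2% | 80.5% | +2.3 | 0.309 |
| 40% | 5 | 79.3% | 83.7% | +4.4 | 0.281 |
| 40% | 8 | 78.3% | 86.6% | +8.3 | 0.249 |

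Type I error was 4.1 to 5.0% without the covariate and 4.6 to 5.7% with it. The Monte Carlo standard error of one power figure is about √(0.8×0.2/4000) = 0.6 points, so differences of a few tenths are noise.

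**Step 3: a continuous covariate with the stratifiers in both models.** Six-month pain is a latent normal variable cut to give 50% and 25%. Six centers and axillary dissection are in both models; 55 per arm, 4,000 trials, Wald test. The latent correlation with T0 pain is assumed.

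- Correlation 0.3: 77.3% to 79.0% (+1.7 points).
- Correlation 0.4: 76.1% to 80.6% (+4.5 points).
- Correlation 0.5: 77.8% to 84.0% (+6.2 points).
- Correlation 0: 77.1% and 76.9%, no material difference.
- Null case at correlation 0.4: 5.6% rejections in both models.

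**Step 4: chance imbalance.** With 55 per arm, the arms differ by 10 points or more in T0 pain in about 19% of trials if the share is 20%, and in about 29% if it is 40%.

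Take a 40% share and OR 5. In the control arm the risks are about 35% without T0 pain and 73% with it, since 0.6×0.348 + 0.4×0.727 = 0.50. A 10-point imbalance therefore moves the arm's expected prevalence by 0.10 × (0.727 − 0.348) = 3.8 points. That is small beside a 25-point effect, but it can matter near the significance boundary.

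**Step 5: what happens to the OR.** 50% versus 25% is a marginal OR of (0.25/0.75)/(0.50/0.50) = 0.333 and a risk ratio of 0.5. With the marginal rates unchanged, conditioning on T0 pain moves the OR to 0.25 to 0.27 when T0 pain has OR 8 (last column above). The adjusted OR is then no longer the quantity implied by the sample size section.

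**The case against.** Adjusting for the stratification factors is a legitimate, pre-specified analysis, and most of the case against a stronger reading stands.

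- **Validity.** A reader might infer that the omission biases the result. It does not. Randomization protects the comparison, type I error is near 5% either way, and chance imbalance is already reflected in the CI and p-value.
- **Hidden effect.** A reader might infer that reporting an OR conceals the halving of prevalence on which the trial was sized. The same section reports prevalence by arm, so the crude difference and ratio can be read off. Only an adjusted version with a CI is not mentioned.
- **Most important predictor.** A reader might take the background to single out breast pain. It speaks of pre-existing pain in general, among several factors, and Table 2 records pain elsewhere separately. Axillary dissection, another listed factor, is already adjusted for.
- **New versus existing pain.** Adjustment does not separate them. A patient with a score of 3 or more both before surgery and at six months is still a case.
- **Size.** The gains depend on associations that the documents do not give. A latent-normal run assuming that 80% of patients score 0 at T0 (2,000 trials, no stratifiers) gives only +0.6, +1.3, +2.9 and +3.4 points at correlations 0.2, 0.3, 0.4 and 0.5.
- **Reserve.** The simulations use 55 per arm. With all 69 per arm evaluable, the pooled formula gives about 87% power, and section {21b} allows the sample size to be recomputed.

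This reduces the weight of the point but does not remove it. The covariate set is stated in the article rather than left open, the score is on the endpoint's own scale and site, and including it costs essentially nothing if it proves uninformative.

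**Conclusion.** The point holds as one of efficiency and robustness, not validity. The plan leaves unused a baseline score that it collects on the same scale and site as its endpoint.

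At 55 per arm, adding it is worth about 0 to +2 points of power for a weak to moderate association (OR up to 3, or latent correlation about 0.3). For a strong one (OR 5 to 8, or latent correlation 0.4 to 0.5) it is worth about +4 to +8 points, but nearer 3 if most patients have no pain at T0. With no association nothing material is lost, and type I error stays near 5%. All these associations, and the shares with T0 pain, are assumptions.

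The documents do not support saying that the planned analysis is invalid, that the effect on prevalence is concealed, or that adjustment would make this a trial of new-onset pain.

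**What to change.** Before unblinding, pre-specify the T0 NRS of the operated breast, as a continuous term, in the primary logistic model alongside axillary dissection and center. The T0 window overlaps that of the first online session in Table 1 (1–2 weeks before surgery), so state that the value used is the one recorded before allocation.

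Because the added covariate changes the conditional OR, also report the standardized risk difference and risk ratio with 95% CI from the same model, next to the OR and the arm prevalences already planned.

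The cost is a line or two in the analysis plan and one more model parameter. No new data and no change in sample size are needed.
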